### Data management

Data from participating patients are documented in eCRFs and captured in the REDCap Cloud Electronic Data Capture system (https://www.redcapcloud.com/). CRFs are to be completed in a timely manner and are password protected—only authorised personnel have access. After termination of the registry, each site will receive an electronic copy of its own data.

Images collected in association with this study will be de-identified and sent to the sponsor digitally.

Due to the observational nature of the study, a data monitoring safety board has not been implemented. Regular data monitoring and cleaning will be performed to ensure data accuracy.

### Current study status

Currently, 12 sites are participating in the study, with the majority being European sites. These sites are summarised in table 1. The first patient enrolment was in December 2019. The initial analysis of the study is expected to be completed by mid-2026.

## Discussion

Within the CMF community, there is a lack of consensus on OFx treatment strategy, including which symptoms and/or radiological parameters warrant a surgical versus non-surgical treatment approach. There is also a lack of consensus regarding the optimal surgical technique and best timing of the surgical intervention. This study protocol describes the collaborative efforts for evidence-based research on treatment management of orbital floor and/or medial wall fractures and factors which may influence clinical outcomes and safety measures.

The OFx Registry will prospectively collect multicentre data on a large, international, observational cohort within a real-world setting. The aim will be to detect meaningful, hypothesis-generating patterns in surgical versus non-surgical treatments and outcomes. Analyses of the OFX Registry data may help provide a valuable evaluation and documentation of OFx management to aid clinicians in implementing evidence-based protocols and minimising bias within standard of care. With a planned sample size of approximately 300 patients, the registry will offer sufficient statistical power for meaningful subgroup analysis, hypothesis generation and generalisability.

Limitations of the observational study design include the lack of randomisation and lack of a control group, which limits the ability to establish causality or directly compare treatment effectiveness. Additionally, given the multicentre participation in the study, there may be variance in data quality and/or different management trends observed between sites and between different regions, thus complicating the interpretation of outcomes. The strengths of multicentre data outweigh this limitation, however, as multicentre research enables a greater sample size and may provide greater clinical translation and application to a broader patient population across diverse clinical settings. If variability including clinician/geographical bias is detected during analyses, this may help to develop guidelines and a cost-benefit analysis to OFx management. Given the observational design, some bias of treatment strategy is expected and will be analysed and discussed in peer-reviewed publications stemming from the OFx Registry, for example, topics such as fracture severity based on recorded fracture details. Lastly, the absence of a standardised imaging protocol across sites due to the non-interventional design also poses challenges, as differences in imaging quality, timing and availability may affect data consistency.

This study protocol also describes how the OFx Registry may help to partially validate the AO CMF Injury Symptom Battery questionnaire as a newly established PRO. With the overarching aim within clinical care toward patient-centric, holistic approaches, it is critical for clinical research to measure PROs that impact recovery and daily quality of life, for example, occurrence and severity of pain and discomfort in daily tasks. Via a survey study between CMF surgeons and other sampled surgical fields, Joeris *et al* 2018 demonstrated that CMF surgeons are less familiar with PROs and use PROs less often as a study outcome, perhaps due to the lack of an established PRO specific to CMF traumatic injuries.^28^ The AO CMF Injury Symptom Battery questionnaire provides clinicians with a useful tool for assessing clinical outcomes from the patient perspective. Along with the need for psychometric validation, the limitation of the questionnaire is it is currently only available for English-speaking sites, and thus, results will have limited validity. Further studies with translated questionnaires in other languages will need to be performed to increase the validity of the tool. In the current study, only two of the nine modules described in the PRO were assessed, so further studies are required as well with all modules implemented. There was also no direct patient involvement for protocol development, so there may be measures important to patients that are missing from the registry. For the current study protocol, these limitations of the PROs will not have a significant impact on the quality of research outcomes.

This protocol defines the cooperative, multicentre effort of the OFx Registry Group to provide an open-ended, exploratory database for identifying OFx treatment trends and outcomes. The study will generate hypotheses for future research with the aim to standardise safe and effective OFx management of the highest clinical benefit.

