**Trial registration number:**

NCT03887988.

STRENGTHS AND LIMITATIONS OF THIS STUDYThe study protocol describes a prospective, international, multicentre registry collecting observational, real-world data from a large cohort of patients with fractures of the orbital floor and/or medial wall.By documenting routine standard of care of orbital fractures without intervention, the study will reflect real-world treatment patterns and clinical outcomes across diverse clinical settings.With a planned sample size of approximately 300 patients, the study will have sufficient statistical power for meaningful subgroup analysis, hypothesis generation and generalisability.Limitations of the observational study design include the lack of randomisation and lack of a control group, which limits the ability to establish causality or directly compare treatment effectiveness.Variability in treatment decisions across clinicians and geographical sites may lead to heterogeneity in the data and complex data interpretation but will potentially allow for extensive subanalyses and characterisation of related factors.

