## Methods and analysis

### Study design and setting

This is a prospective, multicentre, international, observational cohort study serving as a registry for OFx treatment. Table 1 summarises the sites that are currently included in the study. All sites are academic tertiary care medical centres.

**Table 1 T1:** Details of participating sites

Participating site	Country	Region
Universitätsspital Basel	Switzerland	Europe
University of Belgrade	Serbia	Europe
Hamad Medical Corporation	Qatar	Middle East
King Edward VIII Hospital	South Africa	Africa
Medizinische Hochschule Hannover	Germany	Europe
Rambam Health Care Campus	Israel	Middle East
12 de Octubre University Hospital	Spain	Europe
National Medical and Surgical Center named after N.I. Pirogov	Russia	Europe and Asia
Ludwig-Maximillians-Universität – Klinikum der Universität München	Germany	Europe
Federico II University of Naples Italy	Italy	Europe
Erasmus University Medical Center	Netherlands	Europe
University of California, Davis	USA	North America

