### Study design

This observational study protocol does not dictate any study-specific treatments, selection of materials or surgical techniques. All treatments will be performed according to the usual practice at participating sites and determined by the treating surgeons. Patients will be allocated to either the surgical or non-surgical group based primarily on local standard of care practices. This decision will be guided by the treating clinician’s judgement and relevant clinical indications, including individual patient characteristics and patient willingness to receive treatment. Post-treatment care and follow-up visits will also be conducted according to the standard procedures at participating sites.

Non-surgical treatments include either observation only, that is, no treatment or specific measures given, or conservative treatment with the use of supportive measures, for example, local antibiotics, anti-inflammatories, cold compresses and head elevation.

Primary surgical treatments will be classified as either ‘early’ or ‘delayed’ surgery when performed at ≤3 weeks or >3 weeks after the injury, respectively. Secondary reconstructions following unsuccessful primary surgical treatments of OFx will also be included in the study.

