#### Recruitment

The recruitment period will be ~36 months, during which approximately 300 patients are planned to be enrolled.

The participating sites will identify all consecutive eligible patients according to the defined inclusion and exclusion criteria. Eligibility assessment will be performed by the investigator and/or adequately trained member(s) of the research team. The assessment of eligibility includes but is not limited to an inquiry about the interest and willingness of the patient to participate in the research project. Data collection for this registry is not allowed without the consent of the patient or surrogate, and therefore, no data are collected in the electronic case report form (eCRF) prior to obtaining consent by the patient.

All consented patients will be allocated to a unique patient number. Each site will keep an Identification List linking the patient number with his/her personal information. Such Identification List is kept safe and in a locked place always. Sites are not allowed to share the Identification List with any third party except for the sponsor representative, legal authorities and EC/IRB, who may have access to the Identification List during monitoring/auditing activities performed on-site.

All consented patients should be followed up within the registry, except if their study participation is prematurely terminated.

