### Statistical analysis

This is a registry-style observational study that aims to increase our knowledge about the treatment and outcome of OFx. Therefore, there is no formal statistical hypothesis and no formal sample size calculation. However, a detailed statistical analysis plan will be prepared before the final analysis documenting the descriptive statistics to be used for data assessment.

As the aim of the current registry is mainly descriptive, the patient characteristics, clinical data and outcomes recorded at routine standard of care scheduled follow-up assessments will be presented using simple summary statistics. Categorical variables will be summarised using the frequency and percentage for each category. Continuous variables will be summarised using the mean, SD, median, IQR, and minimum and maximum. Additionally, these summary statistics will be presented according to clinically relevant categories, for example, according to treatment received (conservative vs surgical treatment). Depending on the volume and the quality of the collected data, further appropriate statistics will be applied.

The AEs will be summarised both at patient level and AE level. AE rates with 95% CIs will be calculated based on the total population size, irrespective of dropouts during follow-up.

In general, all enrolled and eligible patients who were treated within the registry will be included in the analysis. If a patient discontinues participation due to any reason, all data collected before discontinuation will be integrated into the analysis. For specific research questions, only certain subgroups of patients may be relevant. In such a case, prior to the analysis, it will be defined which patients will be included in the analysis. Details concerning the handling of missing data and protocol violations will be specified in the statistical analysis plan.

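### The article twice claims adequate power for subgroup analysis and generalisability, but it gives no basis for the claim and its own statistics section contradicts it

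*Protocol article*

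**What the plan says.** The Recruitment section states that "approximately 300 patients are planned to be enrolled". Two places then attach a power claim to that number. In the Strengths and limitations box (printed under the trial registration number), "the study will have sufficient statistical power for meaningful subgroup analysis, hypothesis generation and generalisability". In the Discussion, "the registry will offer sufficient statistical power for meaningful subgroup analysis, hypothesis generation and generalisability".

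The Statistical analysis section takes a different position: "there is no formal statistical hypothesis and no formal sample size calculation". It continues: "As the aim of the current registry is mainly descriptive", simple summary statistics will be used. The only inferential quantity it names is for adverse events: "AE rates with 95% CIs will be calculated based on the total population size, irrespective of dropouts during follow-up".

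On treatment groups, the Study design section says: "Patients will be allocated to either the surgical or non-surgical group based primarily on local standard of care practices". No split is forecast. Primary surgery is further divided into early and delayed, and secondary reconstructions are also included. On setting, Study design and setting says: "All sites are academic tertiary care medical centres".

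**The concern.** Power is the probability that a given test, at a given significance level and with given group sizes, detects a given effect. The article specifies none of these, yet calls the power sufficient and lists it as a strength. A registry may do without a power calculation. What it cannot do is assert the result of one that was not formally made.

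What is at stake is how subgroup results are read. The second objective includes comparing surgical with non-surgical outcomes, and the article foresees extensive subanalyses. A reader who accepts the power statement may take a null subgroup result as evidence of no difference, or give a chance finding more weight than it deserves.

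The sentence also treats generalisability as something that sample size provides. Generalisability depends on which sites and patients enter the study.

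**Working it through.** **1. Can the claim be reproduced?** No. The article supplies the total (about 300), the number of sites (12, so 300/12 = 25 per site on average) and a 95% confidence level for adverse event rates. It supplies no effect, event rate, standard deviation, test level, target power, treatment split, subgroup size or dropout rate. There is no power figure to check.

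**2. Sensitivity, under assumptions that are not in the article.** Two-sided 5% test of two proportions, 20% versus 35%, n per group. The mean proportion is 0.275.

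Power = Φ[(0.15 − 1.96·SE0)/SE1], with SE0 = √(2·0.275·0.725/n) and SE1 = √((0.20·0.80 + 0.35·0.65)/n).

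- n = 150: SE0 = 0.0516, SE1 = 0.0508, power 83%
- n = 75: SE0 = 0.0729, SE1 = 0.0719, power 54%
- n = 50: SE0 = 0.0893, SE1 = 0.0880, power 39%
- n = 25: SE0 = 0.1263, SE1 = 0.1245, power 22%

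**3. How far this depends on the assumptions.**

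- *Direction.* Starting from 20%, the difference detectable with 80% power is 14.3, 20.9 and 26.0 points for an increase at 150, 75 and 50 per group. For a decrease it is 11.3, 15.0 and 17.5 points.
- *Split.* With 240 versus 60 in place of 150 versus 150, the detectable increase rises from 14.3 to 17.7 points.
- *Favourable case.* For a standardised difference of 0.5 in 75 versus 75, power = Φ(0.5·√(75/2) − 1.96) = Φ(1.10), or about 86%.
- *Interaction.* For a treatment-by-subgroup test in all 300 with four equal cells of 75, the detectable standardised difference is 2.8·√(4/75) = 0.65.

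None of these figures allows for confounder adjustment or multiplicity.

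**4. Precision, which a descriptive registry can state.** The 95% half-width for a proportion of 50%, with independent and fully observed patients, is 1.96·√(0.25/n):

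- n = 300: 5.7 points
- n = 50: 13.9 points
- n = 25: 19.6 points

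With 20% dropout (assumed; 240 evaluable) the first figure becomes 6.3 points. With an assumed intraclass correlation of 0.05 and 25 patients per site, the design effect is 1 + 24·0.05 = 2.2, the effective n is 300/2.2 = 136, and the half-width is 8.4 points.

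**5. Generalisability.** No calculation applies. A larger sample from the same kind of centre gives more precise estimates for that kind of centre and does not extend the result to others.

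**The case against.** The best defence is that the article is modest elsewhere. It calls its aim mainly descriptive and its database exploratory, and it says that the design limits direct comparison of treatment effectiveness. No endpoint, analysis or decision rule depends on the power sentence. This stands, and it is why the repair is one of wording.

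Three further points also stand. Generating hypotheses needs no formal power, so that part of the sentence does little harm. The article denies only a *formal* sample size calculation, so one should not say that no sizing of any kind was considered. And every power figure above rests on assumed rates and group sizes.

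A reader might infer that 300 patients cannot give adequate power in any subgroup. The document does not support that. It fixes neither effects nor subgroup sizes, and the favourable case above exceeds 80%. A reader might also apply the effective sample size of 136 to the surgical versus non-surgical comparison. It describes an overall estimate; treatment is chosen patient by patient within sites, so a within-site comparison need not lose that much. Finally, the article's talk of diverse clinical settings might look like a contradiction of its all-tertiary site list. That phrase lies outside the power sentence and can fairly mean geographic diversity, since Table 1 lists 12 sites in 11 countries.

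The defence does not reach the claim itself. A statistical analysis plan not shown here cannot excuse it, because the article asserts the power and its own statistics section removes the basis.

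**Conclusion.** The power claim is unsupported and inconsistent with the Statistical analysis section. That conclusion needs no assumed number. The further conclusion, that adequate power is doubtful for many plausible subgroups, does rest on assumptions: at 20% versus 35%, power falls below 80% well before groups shrink to 75 and is about one in five at 25 per group. Large effects in large, balanced subgroups could still be detected, so inadequacy across the board is not shown. The generalisability claim does not follow from power, and the site list limits it to academic tertiary centres.

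**What to change.** Delete the power claim in both the Strengths and limitations box and the Discussion. In its place, state that no formal power calculation was made, that subgroup comparisons are exploratory and reported as estimates with 95% confidence intervals, and that the results generalise to academic tertiary centres.

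If precision is quoted, give its assumptions alongside. For independent, fully observed patients and a proportion of 50%, the half-width is about 5.7 points for 300 patients, 13.9 for 50 and 19.6 for 25. Add that dropout and clustering by site widen these intervals. The 5.7 points must not be presented as an upper limit.

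The cost is a few sentences and the loss of a favourable statement. No data collection, sample size or planned analysis changes.

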## Ethics and dissemination

Ethics approval was obtained from the local ethics committee or institutional review board prior to patient enrolment.

The ethics committees and reference numbers (Ref. No.) for the OFx study are as follows: Ethikkommission Nordwest- und Zentralschweiz (Ref. No. 2019–01648); Ethic Committee of the School of Dental Medicine University of Belgrade (Ref. No. No 36/18); Institutional Review Board Hamad Medical Corporation Doha - Qatar (Ref. No. MRC-01-19-402); Biomedical Research Ethics Committee, University of Kwazulu-Natal (Ref. No. BE468/19); Rambam Medical Center Institutional Review Board (Ref. No. 0114–20-RMB); Comité de Ética de la Investigación con medicamentos del Hospital Universitario 12 de Octubre (Ref. No. 19/292); Local Ethical Committee of Federal State Budgetary Institution ‘National Medical & Surgical Center named after N.I. Pigrogov’, Ministry of Health of the Russian Federation (Ref. No. not applicable); Ethikkommission Medizinische Hochschule Hannover (Ref. No. 11454_BO_K_2024); Ethikkommission bei der LMU München (Ref. No. 19–580); Comitato Etico Universita Federico II (Ref. No. 245/20); Medische Ethische Toetsings Commissie Erasmus MC (Ref. No. MED-2019–0587); and UC Davis Institutional Review Board (Ref. No. 1470876).
